#### **6. End points**

Shorthand for antibody measures:

- IgG to Pertussis antigens: **PT, PRN, FHA, FIM2, FIM3**

- Polio Titre to serotypes 1,2,3: **Polio1, Polio2, Polio3** (also **PolioX\_8** for  $\geq 8$ )
- Anti-tetanus toxoid IgG: **TT** (Also **TT0.10 TT1.00** mean conc  $\geq 0.10$  and  $\geq 1.00$ )
- Anti-diphtheria toxoid IgG: **Dip** (Also **Dip0.10 Dip1.00** mean conc  $\geq 0.10$  and  $\geq 1.00$ )
- Anti-PRP IgG: **Hib** (Also **Hib0.15 Hib1.00** mean conc  $\geq 0.15$  and  $\geq 1.00$ )
- Meningococcal serogroup C serum bactericidal antibody titre : **SBA** (Also **SBA8, SBA128** for  $\geq 8$  and  $\geq 128$ )
- meningococcal serogroup C-specific IgG: **MenC**
- Serotype-specific pneumococcal IgG for 13 vaccine serotypes: **Pn\_x** (where x is the serotype).
- Functional pneumococcal antibody level: **Pn\_fun\_x** (where x is the serotype)

The end points are labelled to match the objectives.

### 6.1 Primary end point

**PE:** Fold change in PT from blood taken at 2 to 5 months (post primary vaccination) in infants of vaccinated mothers.

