#### **2. Objectives**

##### **2.1 Primary**

**PO:** To compare anti-pertussis toxin (PT) IgG responses following primary immunisation with an acellular pertussis- containing vaccine in infants born to mothers who received REPEVAX in pregnancy compared to infants whose mothers received BOOSTRIX-IPV in pregnancy.

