##### **2.2 Secondary**

###### ***Infant***

**SI1:** To compare antibody responses to pertussis antigens (concentration of IgG antibody to PT, pertactin (PRN), filamentous haemagglutinin (FHA) and fimbrial antigens 2 and 3 (FIM 2 and 3)), tetanus toxoid, diphtheria toxoid and polio serotypes 1, 2 and 3 at birth amongst infants born to mothers who received REPEVAX in pregnancy compared to infants whose mothers received BOOSTRIX-IPV in pregnancy

**SI2:** To compare antibody responses to pertussis antigens [IgG to PT, PRN, FHA and FIM 2 and 3], Hib antigen [PRP], tetanus toxoid, diphtheria toxoid and polio serotypes 1, 2 and 3; meningococcal serogroup C serum bactericidal antibody titres and meningococcal serogroup C-specific IgG concentrations; 13 serotype-specific pneumococcal IgG concentrations and functional pneumococcal antibody studies at 2, 5 and 13 months of age (just before and one month after primary immunization and one month after booster vaccines) in infants born to mothers who received REPEVAX in pregnancy compared to infants whose mothers received BOOSTRIX-IPV in pregnancy and compared to infants whose mothers who did not receive pertussis vaccination in pregnancy

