## **3. Design**

Full details are in the study protocol. Briefly women will be recruited at two sites during routine antenatal appointments and randomised to receive either REPEVAX or BOOSTRIX in pregnancy. A separate group of women who did not receive vaccination in pregnancy will be recruited at post natal visits as a control group.

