### **3.1 Study schedule**

| Visit                                 | V1
Pregnancy                  | V2
Birth                | V3
2 months       | V4
3 months           | V5
4 months           | V6
5 months           | V7
12 months     | V8
13 months          |
|---------------------------------------|----------------------------------|----------------------------|----------------------|--------------------------|--------------------------|--------------------------|---------------------|--------------------------|
| Visit Window                          | 28-32 weeks                      | 0-7 days hours after birth | 49-84 days of age    | 21-42 days after visit 3 | 21-42 days after visit 4 | 21-42 days after visit 5 | 353-390 days of age | 21-42 days after visit 7 |
| Vaccinated mothers:                   | REPEVAX/BOOSTRIX-IPV
Blood MA | Blood MB                   |                      |                          |                          |                          |                     | Blood MC                 |
| Unvaccinated Mothers                  |                                  |                            |                      |                          |                          |                          |                     | Blood MC                 |
| Infants born to vaccinated mothers:   |                                  | Blood BA                   | Routine*
Blood BB | Routine*                 | Routine*                 | Blood BC                 | Routine*            | (MMR**) Blood BD         |
| Infants born to unvaccinated mothers: |                                  |                            | Routine*
Blood BB | Routine*                 | Routine*                 | Blood BC                 | Routine*            | (MMR**) Blood BD         |

\*routine schedule is 2m: Infanrix/Prev13/Bexsero/Rotarix, 3m: Infanrix/MenC (Neis)/Rotarix, 4m: Infanrix/Prev/Bexsero, 12m: Menitorix/Prev/Bexsero/MMR. \*\*MMR can be given at 12m or at 13m.

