#### **4. Sample Size**

Based on sample size calculations below, it is proposed that a convenience sample of 65 (+/-10) mother-infant pairs will be recruited into each of the two groups that received a pertussis vaccine in pregnancy, with a control group of 30 (+/-10) women and their infants. Up to 200 mother-infant pairs will be recruited to take account of mother-infant pairs lost to follow-up.

The sample size calculation is based on data from the recent P13UK study performed by PHE. Based on these results, the standard deviation of the post-primary vaccination GMCs (log-10 scale) was: PT = 0.28, Hib = 0.76, MenC SBA = 0.50, Tet = 0.37. Based on these SD with 65 per study arm fold differences of 1.38, 2.37, 1.77 and 1.52 would be detectable between the vaccine arms for PT, Hib, MenC and Tet respectively. In terms of percentages reaching putative protective levels 95% in one arm would be different to percentages below 77% in the other arm. The protocol has more details on other sample sizes.

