### 6.2 Secondary end points

**SI1:** In the infant at birth (just vaccinated mothers group) - PT, PRN, FHA, FIM2, FIM3, TT (TT0.10/TT1.00) ,Dip (Dip0.10/Dip1.00).

**SI2:** In infants at 2,5 and 13 months (all groups) PT, PRN, FHA , FIM2, FIM3, Hib (Hib0.15, Hib1.00), TT (TT0.10/TT1.00) ,Dip (Dip0.10/Dip1.00), SBA (SBA8, SBA128), MenC, Polio1, Polio2, Polio3 (PolioX\_8), Pn\_x, Pn\_fun\_x.

**SM1:** In Mothers pre vaccination and at delivery (just vaccinated mothers group) - PT, PRN, FHA, FIM2, FIM3, TT (TT0.10/TT1.00) ,Dip (Dip0.10/Dip1.00).

**SM2:** In Mothers/Babies (cord blood) at delivery (just vaccinated mothers group) ratio of Baby to Mother PT, PRN, FHA, FIM2, FIM3, TT (TT0.10/TT1.00) ,Dip (Dip0.10/Dip1.00).

**SM3:** In Mothers (all groups) at 13 months: PT, PRN, FHA, FIM2, FIM3. (And for vaccinated mothers ratio with levels at delivery).

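### The primary end point divides 5-month PT by a 2-month PT that the randomised maternal vaccine can itself change, and the sample size was worked out for the 5-month level instead

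*SAP*

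**What the plan says.** The primary objective in SAP section 2.1 is "To compare anti-pertussis toxin (PT) IgG responses following primary immunisation" in infants of mothers given one or the other vaccine. It names no metric. Section 6.1 supplies one: "Fold change in PT from blood taken at 2 to 5 months (post primary vaccination) in infants of vaccinated mothers". Section 10.4 log-transforms ratios and compares the arms by normal-errors regression, which for two groups is an unpaired t-test with no covariates.

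The order of events matters. Section 3 says that women are "randomised to receive either REPEVAX or BOOSTRIX in pregnancy", and the schedule in section 3.1 puts that visit at 28 to 32 weeks. The infant bloods follow. Section 2.2 (SI2) describes the 2-, 5- and 13-month samples as taken "just before and one month after primary immunization and one month after booster vaccines", so the 2-month sample precedes infant immunisation but follows the randomised intervention. Section 6.2 lists 2-month PT as an outcome in its own right: "In infants at 2,5 and 13 months (all groups) PT, PRN, FHA , FIM2, FIM3". PT at birth (SI1) and placental transfer (SM2) are also compared between the randomised arms.

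The sample size in section 4 rests on a different quantity: "the standard deviation of the post-primary vaccination GMCs (log-10 scale) was: PT = 0.28". From this and 65 per arm the SAP gives a detectable PT fold difference of 1.38. It gives no SD for the 2-month level, none for the change from 2 to 5 months, and no correlation between the two.

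**The concern.** In most vaccine trials the pre-vaccination sample is a baseline that treatment cannot have affected, and dividing by it does no harm to the between-arm comparison. Here the randomised treatment is given to the mother in pregnancy, so the infant's 2-month antibody is one of its results. The primary end point then combines two arm effects with opposite signs: more antibody at 5 months raises it, and more antibody at 2 months lowers it. A lower fold change in one arm could mean a weaker infant response, or only that its infants started with more maternal antibody. The SAP does not say how the second case is to be read.

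The power statement is a separate matter. It describes the 5-month concentration, so the trial's ability to detect a difference in its declared primary end point is not stated.

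**Working it through.** **Inputs from the SAP.** 65 per arm and SD of log10 post-primary PT of 0.28 (section 4); 5% significance level (section 10.2). Two-sided testing is assumed. Power is not stated in the SAP; 80% is inferred because it reproduces the stated figures.

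**Step 1: reproduce the plan's figure.** The standard error of the difference in log10 means is 0.28 × √(2/65) = 0.0491. The detectable ratio at 80% power is 10^[(1.960 + 0.842) × 0.0491] = 1.37, or 1.38 with the t distribution. Power at 1.38 is Φ(log10 1.38 / 0.0491 − 1.960) = Φ(0.1399/0.0491 − 1.960) = 81%. The same method gives 2.36, 1.76 and 1.52 for Hib, MenC and tetanus (2.38, 1.77 and 1.53 with t), against the stated 2.37, 1.77 and 1.52. So 1.38 is correct, for the 5-month concentration.

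**Step 2: what the fold change compares.** On the log scale,

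log(fold-change ratio) = log(5-month GMC ratio) − log(2-month GMC ratio).

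The fold-change ratio is therefore the 5-month GMC ratio divided by the 2-month GMC ratio. It falls below 1 whenever an arm's advantage at 2 months exceeds its advantage at 5 months, even if that arm is higher at both times.

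**Step 3: power for the end point as written.** The SD of the log10 change is √(SD5² + SD2² − 2ρ·SD5·SD2), with SD5 = 0.28. SD2 and ρ are assumptions.

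| SD2 (assumed) | ρ (assumed) | SD of change | Detectable ratio, 80% power | Power at 1.38 |
|---|---|---|---|---|
| 0.28 | 0.5 | 0.28 | 1.37 | 81% |
| 0.28 | 0 | 0.40 | 1.57 | 52% |
| 0.40 | 0.5 | 0.36 | 1.50 | 61% |
| 0.40 | 0 | 0.49 | 1.74 | 37% |
| 0.50 | 0 | 0.57 | 1.91 | 29% |
| 0.50 | −0.4 | 0.66 | 2.12 | 22% |

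Within the range examined (SD2 0.28 to 0.50, ρ −0.4 to 0.5), the stated 1.38 survives only in the first row. A correlation above 0.5 would reduce the loss.

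**Step 4: what a 2-month difference would do.** The SAP gives no expected 2-month ratio, so these are illustrations. The last column uses three assumed pairs (SD2, ρ): (0.28, 0), (0.40, 0) and (0.40, −0.3).

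| 2-month ratio A/B | 5-month ratio A/B | Fold-change ratio A/B | Chance of a significantly lower fold change in A |
|---|---|---|---|
| 1.5 | 1.0 | 0.67 | 72%, 54%, 44% |
| 1.5 | 1.2 | 0.80 | 29%, 20%, 17% |
| 2.0 | 1.38 | 0.69 | 64%, 47%, 38% |
| 1.0 | 1.38 | 1.38 | not applicable: equals the 5-month ratio |

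In the second and third rows arm A has more antibody at both times and the lower fold change. In the last row, with equal 2-month levels, the fold change and the 5-month level estimate the same ratio.

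**The case against.** The strongest reply is that nothing here is biased. Fold change is an outcome measured after randomisation, compared without conditioning on anything, and its arm difference is a proper randomised effect. That stands. A reader might take the percentages in step 4 for false-positive rates; they are not. They are the power to detect a real difference in the declared end point. What is in doubt is what such a difference would mean.

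Fold change may also be intended, as a measure of how far maternal antibody blunts the infant's response. The objective's wording does not exclude it, and the protocol, which holds the full rationale, is not at hand. But the SAP states no such aim, and SI1 and SI2 use the word responses for antibody levels at single time points.

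The SAP also has much of the safeguard already. SI2 covers PT at 2 and 5 months, section 10.4 requires geometric means and between-group ratios with confidence intervals, and section 10.5 plans to relate the 2-month titre to later responses. An attentive reader could thus see what drove the fold change, and it would go too far to say that a null result conceals offsetting effects. Still, these are secondary or exploratory analyses, and nothing says they must be read with the primary result. Adjusting for 2-month PT would be no neutral cure either, because it conditions on something the randomised vaccine may have changed.

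A reader might also infer that the width of the 2-month visit window ("49-84 days of age") distorts the denominator. The window is the same in both arms, so it adds variance and not expected bias, and the SAP gives no decay rate from which to size it. Nor may 1.38 be used as an expected 2-month difference: section 4 gives it for post-primary PT only.

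Finally, the 5-month level may itself contain some residual maternal antibody. That is true, and it limits what any 5-month end point can say about the infant's own response.

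**Conclusion.** The point holds in a limited form. The primary comparison is valid as a randomised comparison, but alone it cannot distinguish an effect of the maternal vaccine on passive antibody from an effect on the post-primary level, and it can rank an arm lower that has more antibody at both times. That follows from the definition and needs no assumption. Whether it happens, and how strongly, depends on a 2-month arm ratio, a 2-month SD and a correlation that the SAP does not give. The documents therefore do not support a claim that the primary result will be reversed.

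The mismatch with the sample size is firm: the 1.38 belongs to the 5-month concentration. Under the assumed ranges the detectable fold-change ratio is about 1.37 to 2.12, and power at 1.38 lies between 81% and 22%.

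**What to change.** Before data are supplied, make log10 PT IgG at 5 months (blood BC) the primary end point, compared between the randomised arms as a GMC ratio with 95% CI. Keep the 2-to-5-month fold change as a secondary end point, reported beside the 2-month and 5-month GMC ratios. The primary test then matches the sample-size basis, and 1.38 stands as written.

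If the protocol intends fold change as primary, keep it, but state that aim in the SAP, require the result to be read with both GMC ratios, and restate the detectable difference using an SD of the log10 fold change.

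The cost is small. The 5-month PT is already measured and analysed under SI2, and section 1.3 provides for a final version of the plan before the statistician receives data. If the protocol names fold change, the first option needs a short protocol amendment. The possible residual maternal antibody at 5 months should be acknowledged when the result is interpreted.

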### 6.2 Secondary end points

**SI1:** In the infant at birth (just vaccinated mothers group) - PT, PRN, FHA, FIM2, FIM3, TT (TT0.10/TT1.00) ,Dip (Dip0.10/Dip1.00).

**SI2:** In infants at 2,5 and 13 months (all groups) PT, PRN, FHA , FIM2, FIM3, Hib (Hib0.15, Hib1.00), TT (TT0.10/TT1.00) ,Dip (Dip0.10/Dip1.00), SBA (SBA8, SBA128), MenC, Polio1, Polio2, Polio3 (PolioX\_8), Pn\_x, Pn\_fun\_x.

**SM1:** In Mothers pre vaccination and at delivery (just vaccinated mothers group) - PT, PRN, FHA, FIM2, FIM3, TT (TT0.10/TT1.00) ,Dip (Dip0.10/Dip1.00).

**SM2:** In Mothers/Babies (cord blood) at delivery (just vaccinated mothers group) ratio of Baby to Mother PT, PRN, FHA, FIM2, FIM3, TT (TT0.10/TT1.00) ,Dip (Dip0.10/Dip1.00).

**SM3:** In Mothers (all groups) at 13 months: PT, PRN, FHA, FIM2, FIM3. (And for vaccinated mothers ratio with levels at delivery).

### 6.3. Safety data

Diaries are not being collected. End points will be Any serious adverse event following a vaccine dose (yes/no) and Hospital visit related to a vaccination (yes/no).

## 7. Analysis sets and dealing with missing values and censored data

### 7.1 Analysis sets

Analysis will be as treated for safety data and by modified ITT for immunogenicity data. mITT means an individual must have blood samples with results for inclusion, but will be

included irrespective of interventions received. A per protocol analysis will also be performed if more than 10% of individuals would differ between mITT and per protocol.

Major protocol violations will be documented. These include incorrect vaccine given, vaccines not given and vaccines or blood samples given out of the visit windows.

## **7.2 Dealing with missing values and censored data**

The reason for missing data will be indicated but missing data will not be imputed. Censored data will be given a value half the lower limit and twice the upper limit of the assay.

## **8. Supply of data and locking of the database**

Data will be entered into a database at PHE immunisation dept. This will be transferred to the Statistician through exports to Excel or as ASCII files. The data will then be imported into Stata for analysis. Checks will be performed to ensure correct transfer and the statistician will also perform logical checks of the data. Once satisfactory the database will be locked.

## **9. Interim analysis**

No formal Interim analysis is planned.

## **10. Statistical Methods**

### **10.1 Statistical package**

Stata version 13 or higher will be used.

### **10.2 Significance level and confidence intervals**

95% confidence intervals will be reported. Where comparisons are made between groups a 5% significance level will be used.

### **10.3 Descriptive analysis**

A description of number in the trial and with results at each stage will be produced in a flow chart (consort diagram). Descriptive tables of numbers by age (mother), sex (baby), ethnic group, study site, birth weight, gestational age, gestational age at vaccination, weeks prior to birth of vaccination, timing of blood at birth, receipt of influenza vaccination, breast feeding for first 2 months, and other baseline variables will be produced.

### **10.4 Immunogenicity analysis**

The end points in PE,SI1,SI2,SM1,SM2,SM3 are either concentrations, titres, ratios of concentrations or titres or binary values(for being over a threshold). For concentrations and titres (and ratios of these) results will be log transformed and the groups (REPEVAX vs BOOSTRIX-IPV, OR REPEVAX vs BOOSTRIX-IPV vs Control) compared by normal errors regression (equivalent to ANOVA for 3 groups or an unpaired t-test for 2 groups). Geometric means for each group will be calculated with 95% confidence intervals and Geometric mean fold ratios between groups with 95% CIs. If the log transformed data are not normally distributed then the kruskal-wallis test will be used to compare the groups.

Proportions above titre thresholds will be compared using Fisher's exact test and proportions calculated within groups with 95% exact confidence intervals.

For persistence (SM3) geometric mean fold changes will be calculated with 95% CI.

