### ***Mother***

**SM1:** To determine concentrations of antibodies to pertussis antigens [IgG to PT, PRN, FHA and FIM 2 and 3] and tetanus toxoid, diphtheria toxoid and polio serotypes 1, 2 and 3, in pregnant women prior to administration of the REPEVAX or BOOSTRIX-IPV vaccine and at the time of delivery

**SM2:** To estimate the placental transfer ratio of antibodies to pertussis antigens [IgG to PT, PRN, FHA and FIM 2 and 3] and tetanus toxoid, diphtheria toxoid and polio serotypes 1, 2 and 3, in mothers who received REPEVAX in pregnancy compared to mothers who received BOOSTRIX-IPV in pregnancy

**SM3:** To compare concentrations of antibodies to pertussis antigens [IgG to PT, PRN, FHA and FIM 2 and 3] and polio serotypes 1, 2 and 3 at 12-13 months post-delivery in women who received REPEVAX or BOOSTRIX-IPV vaccine and to those women who did not receive pertussis vaccination in pregnancy

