### **10.5. Additional exploratory analyses**

In regression analyses of titres the effect of titre pre vaccination (at 2m) on post primary responses (at 5m and also 13m to the same and different antigens) will be assessed. Regression models to allow for timing of the blood after primary vaccination (or birth), sex, ethnicity, gestational age at vaccination (or weeks prior to birth), study site, gestational age and birth weight will be fitted to investigate these factors and adjust if necessary.

Prior receipt of pertussis vaccination in pregnancy will be investigated for the pre-vaccination maternal blood.

The association between antibodies at birth in infants and at 2 months will be investigated.

The association between breast feeding and post primary responses.

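### For Hib, MenC and pneumococcal antibodies, the main REPEVAX vs BOOSTRIX-IPV comparisons at 5 and 13 months leave out the infant's 2-month level, a usable baseline already being collected

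*SAP*

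**What the plan says.** SAP section 10.4 takes logs of the levels and has "the groups (REPEVAX vs BOOSTRIX-IPV, OR REPEVAX vs BOOSTRIX-IPV vs Control) compared by normal errors regression". In full, the method is given as "compared by normal errors regression (equivalent to ANOVA for 3 groups or an unpaired t-test for 2 groups". Group is the only term, so the reported geometric mean fold ratios and confidence intervals are unadjusted.

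Section 6.2 (SI2) sets the infant end points: "In infants at 2,5 and 13 months (all groups) PT, PRN, FHA , FIM2, FIM3, Hib (Hib0.15, Hib1.00", and the list goes on to SBA, MenC IgG, pneumococcal IgG and functional pneumococcal antibody. Objective SI2 in section 2.2 places the three samples "just before and one month after primary immunization and one month after booster vaccines". The 2-month blood therefore comes before any infant dose, yet section 10.4 treats its result only as one more end point.

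The maternal and birth measures are narrower. Objective SM1 reads "To determine concentrations of antibodies to pertussis antigens [IgG to PT, PRN, FHA and FIM 2 and 3] and tetanus toxoid, diphtheria toxoid", followed by polio. The SI1, SM1 and SM2 end points in section 6.2 list pertussis antigens, tetanus and diphtheria, and the matching objectives add polio. Hib, MenC and pneumococcal antibodies appear in none of them.

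Section 10.5 does plan regressions on "the effect of titre pre vaccination (at 2m) on post primary responses (at 5m and also 13m to the same and different antigens", but under additional exploratory analyses. A separate list of covariates there (timing, sex, ethnicity, site and others) "will be fitted to investigate these factors and adjust if necessary". That list does not include the 2-month titre.

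**The concern.** SI2 asks, among other things, whether the choice of maternal vaccine changes the infant's response to the other routine vaccines. For antigens outside the maternal vaccine, the 2-month level is antibody present before the infant is immunised, and allocation should not move it. If it predicts the later level, adjusting for it removes variation that has nothing to do with the allocated vaccine and narrows the confidence interval at no cost in data.

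The same adjustment would be wrong for pertussis, tetanus, diphtheria and polio. There the 2-month level is itself an effect of the maternal vaccine, and conditioning on it would remove part of the effect under study. Section 10.5 covers the same and different antigens without drawing this line. The SAP thus leaves open, until data are seen, both whether the 2-month level enters a reported estimate and for which antigens it may.

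**Working it through.** **Inputs**
- SD of the post-primary log10 level: PT 0.28, Hib 0.76, MenC SBA 0.50, Tet 0.37 (SAP section 4).
- 65 infants per randomised arm, with detectable folds of 1.38, 2.37, 1.77 and 1.52 (section 4).
- 5% significance level (section 10.2), taken as two-sided. Section 4 states no power, so 80% is assumed and tested below.
- r, the correlation between the log 2-month level and the log later level of the same antibody: not in the SAP. A range of 0 to 0.5 in absolute value is used.

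**Step 1: reproduce the SAP's figures.** Detectable fold = 10^[(1.960 + 0.842) × SD × sqrt(2/65)]. For Hib this is 10^(2.802 × 0.76 × 0.1754) = 10^0.3735 = 2.36.

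| | SAP | Normal approximation | t-test |
|---|---|---|---|
| PT | 1.38 | 1.373 | 1.376 |
| Hib | 2.37 | 2.363 | 2.379 |
| MenC SBA | 1.77 | 1.761 | 1.768 |
| Tet | 1.52 | 1.520 | 1.525 |

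Agreement is within 0.01, and 90% power does not fit (Hib would be 2.7). The SAP's figures are therefore those of an unadjusted two-sample test at 80% power.

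**Step 2: add the 2-month covariate, two randomised arms.** The residual SD becomes SD × sqrt(1 − r²), with 127 degrees of freedom. The equivalent sample size is 65/(1 − r²) per arm.

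| r | Standard error | Equivalent n per arm | Hib fold | MenC SBA fold |
|---|---|---|---|---|
| 0 | no change | 65 | 2.38 | 1.77 |
| 0.1 | −0.5% | 66 | 2.37 | 1.76 |
| 0.2 | −2.0% | 68 | 2.34 | 1.75 |
| 0.3 | −4.6% | 71 | 2.29 | 1.72 |
| 0.5 | −13.4% | 87 | 2.12 | 1.64 |

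Power at the SAP's Hib fold of 2.37, by the normal approximation, goes from 80% to 82%, 84% and 90% at r 0.2, 0.3 and 0.5.

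**Step 3: where the gain shrinks.** Section 7.2 gives every value below the assay limit half that limit. If most 2-month values of an antibody are censored, the covariate is nearly constant and explains little. The SDs in section 4 are post-primary, and the 13-month sample follows the 12-month booster, so neither the SD nor r at 5 months carries over to 13 months.

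**Step 4: comparison with the control group.** Section 5 may add 18 external infants, with bloods at 4, 5, 12 and 13 months and so none at 2 months. A complete-case adjusted comparison drops them. With 30 own controls the standard error rises by a factor of sqrt[(1/65 + 1/30)/(1/65 + 1/48)] = 0.2207/0.1903 = 1.16. Adjustment recovers this only if sqrt(1 − r²) < 1/1.16, that is |r| above about 0.51. Across the section 4 range, the factor and break-even are 1.25 and 0.60 with 20 own controls, and 1.11 and 0.44 with 40. At r 0.3 with 30 controls the net change is 1.16 × 0.954 = 1.11, an 11% larger standard error.

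**The case against.** The strongest reply is that nothing in section 10.4 is wrong. An unadjusted comparison of randomised arms is unbiased, and analysis of covariance in place of a t-test on secondary end points is a matter of efficiency. That stands and sets the weight of the point.

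A second reply is that section 10.5 already plans the regression, for more antigen pairs than are asked for here. That is true, so what is at issue is its exploratory status and the missing line between antigens, not its absence.

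A third is that the gain is not shown. That stands in part: r is unknown, and up to r 0.3 the standard error falls by less than 5%.

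A fourth is that the antigen split is inferred, since the SAP does not list what the maternal vaccines contain. That is so, but the inference fits every maternal and birth objective. The planned SI2 comparison of 2-month levels between arms will also show whether it is reasonable.

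A fifth is that section 10.4 falls back on Kruskal-Wallis for non-normal data and uses Fisher's exact test for thresholds, neither of which takes a covariate. That stands, and the fix has to say so.

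A reader might also infer that the control-group comparison should be adjusted, because inherited antibody could differ between non-randomised groups and distort the later ratio. The SAP gives no 2-month difference and no slope from which to size such a distortion. Step 4 shows that the adjustment usually costs precision by losing the external infants. Meningococcal outcomes are not assessed in controls at all (section 5).

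**Conclusion.** The point holds as an efficiency improvement to the randomised two-arm comparison of Hib, MenC and pneumococcal levels at 5 and 13 months. It is not a bias or an error. Its size is a 2% to 13% smaller standard error for r from 0.2 to 0.5, and nothing at r 0 or where 2-month values sit mostly at the assay floor. It rests on three assumptions: the inference that allocation does not alter the 2-month level of these antibodies, a correlation the SAP does not supply, and 80% power, which reproduces the SAP's figures. For 13 months the size is not established.

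A reader might infer that precision is lost on every end point concerned. Hib, SBA, MenC IgG, 13 pneumococcal IgG and 13 functional measures at two times make (1 + 1 + 1 + 13 + 13) × 2 = 58. The SAP does not support that reading. It does not say how many serotypes have functional assays (without any, the count is 32), and the count shows where the covariate is available, not where it helps.

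**What to change.** In section 10.4, for Hib, MenC (SBA and IgG) and pneumococcal concentrations and titres, and for REPEVAX vs BOOSTRIX-IPV only:

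- Make the main 5- and 13-month analysis a regression of log level on group plus the log 2-month level of the same antibody. Report the adjusted fold ratio with its 95% CI, and the unadjusted result alongside.
- Keep infants without a 2-month result by using the overall mean plus a missing indicator. Note this as an exception, for a covariate only, to the rule in section 7.2 that missing data are not imputed.
- State that this adjustment is not applied to pertussis, tetanus, diphtheria or polio, because there the 2-month level is itself an effect of the allocated vaccine.
- Leave comparisons with the control group (Hib and pneumococcal only) unadjusted as the main result. An adjusted version in infants with a 2-month result is at most a sensitivity analysis.
- State that threshold proportions stay with Fisher's exact test, and that where the Kruskal-Wallis fallback applies it remains unadjusted.

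The cost is a few sentences and one covariate already measured. The drawbacks are the rule for missing 2-month results and a second column of estimates in the tables.
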